### 2.9 Analysis

#### 2.9.1 Effectiveness

Evaluating our effectiveness objective requires following a treatment policy estimand strategy (59, 60)- that is the effect of access to the Nutrition Now resource regardless of post-enrolment or intercurrent events such as non-compliance or discontinuation. This necessitates that outcome data be collected regardless of level of engagement and assumes that missing data are missing not at random (MNAR). Statistical models appropriate for de facto estimands will thus be used and the effect of MNAR on our effectiveness estimates will be assessed using sensitivity analyses. Confounding due to the non-randomised nature of the study, e.g., household size and income, parental education, ECEC status (public or private), will be assessed and adjusted for using regression models.

The main comparison will be between children and parents given access to all Nutrition Now components and those in the control municipality. Similar estimators of the Nutrition Now effectiveness will be available from comparisons within the intervention municipality since we will have data on approximately 100 parent-offspring pairs completely unexposed to the Nutrition Now resource as a result of the recruitment design (described above). The latter comparisons will improve causal inference by triangulating the evidence from two designs with different sources of bias (61). In this example they act as a sensitivity analysis to assess bias from residual confounding.

The recruitment strategy also creates variation in the number of components of the Nutrition Now resource each observational unit will be exposed to. Combined with the serial data collection points (pregnancy, 6 weeks, 6, 12, 18 and 24 months), we will be able to assess the effectiveness of each component of the resource in addition to duration of access.

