**Figure 2 f2:**
[figure not shown]
Overview of assessments, participants, and types of outcome measures in the mixed methods Hybrid 1 trial of the Nutrition Now project. **(A)** Ethnic minorities invited to participate in qualitative interviews in addition to the assessment that applies to all recruited pregnant women/parents of 0-2 year-olds. **(B)** ECEC staff champions and MCH staff contact persons are appointed staff members invited to participate in short iterative interviews. **(C)** ECEC leaders provide socio-demographic data for the effectiveness evaluation to be assessed at the ECEC level in addition to qualitative interviews.

**Table 1 T1:** Effectiveness, implementation and cost-effectiveness outcomes in Nutrition Now.

Outcomes	Evaluation data	Data collection tool	Level
Effectiveness			
Aspects of child diet quality^1^	Frequency of intake of fruits, vegetables, pulses, and sugary drinks.	Short food frequency web-based questionnaire.	Individual
Breastfeeding^2^	Intention of breastfeeding, exclusive breastfeeding duration and any breastfeeding duration	Short web-based questionnaire	Individual
Child eating enjoyment^2^	Child Eating-enjoyment, reported by parents and ECEC staff	Child eating-enjoyment scale (37)	Individual
Child quality of life^2^	Pediatric Quality of Life Infant Scales	PedsQL (38) – Web-based questionnaire	Individual
Child development^2^	Developmental milestones	Ages and stages (18 months) ASQ3 (39)	Individual
Anthropometric measures (mother, child) ^2^	Weight change in pregnancy, mother’s weight and height, child’s weight and length	Short digital web-based questionnaire	Individual
Pregnancy complications	Preeclampsia, gestational diabetes, preterm delivery		Individual
Maternal diet in pregnancy^2^	Diet quality score	Diet screener, web-based questionnaire	Individual
Maternal quality of life^2^	Satisfaction with life score	SWLS - Satisfaction with life scale (40) – Web-based questionnaire	Individual
Parental meal- and feeding practices^2^	Role modelling, responsive feeding, family meal participation, meal distractions, frequency of home cooking, repeated exposure.	Short digital web-based questionnaire	Individual
ECEC staff meal- and feeding practices^2^	Role modelling, meal practices, repeated exposure, collaboration with parents.	Short digital web-based questionnaire	Individual/organizational

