### 2.8 Data collection

Quantitative and qualitative data will be collected in the different parts of this study (**Figure 2** and **Table 1**).

*Quantitative data* for the effectiveness evaluation will be generated from questionnaires and objective measures. Questionnaire data will be obtained from i) pregnant women and parents of 0-2-years-olds, assessed during pregnancy, at child ages 6 weeks, 6 months, 12 months, 18 months, 24 months and ii) ECEC staff, assessed at baseline (pretest) and after 7 months (posttest).

**Figure 4** provides an overview of the timeline for data collection for effectiveness outcomes for the parental part of the study, and duration of exposure to the Nutrition Now resource according to point of inclusion in the intervention municipality.

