**Figure 4 f4:**
[figure not shown]
Overview of timeline for data collection, and exposure to the Nutrition Now resource (consisting of e-learning resources targeting different phases in a child’s 1000 first days) in the intervention municipality in the effectiveness trial. Pregnant women and parents of children between 0-2 years of age will be recruited from October 2022 until April 2023 through the MCH centre route. Participants will be exposed to age-appropriate content of the Nutrition Now resource and will be asked to respond to successive age-specific digital questionnaires depending on whether they are pregnant or the child’s age. Participants are given access to the Nutrition Now resource after completing the first questionnaire (pretest). ECEC staff will be recruited and complete the pretest questionnaire in September 2022, before getting access to the Nutrition Now-recourse. The post-test ECEC-staff questionnaire will be distributed seven months into the implementation of the intervention.

Consenting pregnant women (at any time during pregnancy), and parents of children between 0-2 years (at any time in this age interval) will first be asked to complete a short digital questionnaire to provide socio-demographic data in addition to expected due date (for pregnant women), or child’s age (for parents). Thereafter they will be asked to complete a second questionnaire tailored to the age of the child. Access to the Nutrition Now resource will be provided when the age-specific questionnaire is completed. The dose and duration of exposure to the Nutrition Now resource will differ between the participants depending on when they enter the study. Only those who are pregnant when entering the study between October 2022 and April 2023 will potentially be exposed to the whole range of intervention content, whereas a 1-year-old whose parent(s) enter the study in the same period, will be exposed to the “Toddlers 1-2 years” component and, if in ECEC, also the “Preschoolers 1+ years” component (**Figure 4**). Two-year-olds recruited at the regular health visit will be given access to the “Toddlers 1-2 years” component after completing the 24 months questionnaire.

ECEC leaders and staff will respond to questionnaires when consenting to participate in the study and seven months after getting access to the Nutrition Now resource.

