## 3 Discussion

There are several potential challenges the project may face. Recruitment of participants and their continued participation is crucial for both the implementation and effectiveness part of this study. To reduce participant burden and maximise retention, we will keep the questionnaires short, easily comprehensible, and easy to complete. To avoid missing all data in the case of partly completed questionnaires, it will be possible to respond to only a few initial core questions, and still participate. Further, selection bias at recruitment between intervention and control sites may bias intervention estimates. In addition, although the original interventions have shown promising results in previous studies, the impact of the interventions might be more modest in a real-life setting. This dilution of intervention effect is a common finding in effectiveness studies and implementation trials (66), however the iterative approach to the implementation in our study is meant to reduce the chance of such dilution (54, 66).

A major strength of this study is the established efficacy in the original four interventions, the co-creation with the municipality, ECECs and MCH undertaken, and the established capacity and networks built by the research team. This experience will help address challenges along the way. The municipality setting and organization of ECEC and MCH are quite similar in all parts of Norway and thus, we expect that our findings related to the implementation will be generalizable to other Norwegian municipalities. Further, focusing on culturally diverse groups both in the effectiveness and implementation part, will render more culturally diverse and sensitive resources for future approaches.

*Nutrition Now* will break new ground by (i) systematically implementing and evaluating cumulative effects of successive dietary interventions in the first 1000 days of life in a real-life context, (ii) maximising interdisciplinary collaboration and integrating an anthropological approach with quantitative methods to truly adapt the intervention to context, (iii) bridging the previously described evidence-to-practice gap through rigorous scientific effectiveness evaluation of municipal implementation, (iv) harnessing the benefits of digital, video-based, technology to optimise access to dietary guidance in the municipalities, and (v) taking advantage of existing settings across sectors in municipal care to secure universal reach.

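### Maternal diet in pregnancy is the only listed pre-access diet measure for the fully exposed group, yet it is classed as an outcome and not named among the confounders for the main comparison

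*Protocol article*

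**What the plan says.** All references are to the protocol article.

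- **Main comparison (2.9.1).** "The main comparison will be between children and parents given access to all Nutrition Now components and those in the control municipality".
- **Who can be fully exposed (2.8, Figure 4 legend and text below it).** "Only those who are pregnant when entering the study between October 2022 and April 2023 will potentially be exposed to the whole range of intervention".
- **Order of pretest and access (Figure 4 legend).** "Participants are given access to the Nutrition Now resource after completing the first questionnaire (pretest"). Section 2.8 has control participants fill in the same questionnaires without access.
- **Schedule for parents (2.8).** They are "assessed during pregnancy, at child ages 6 weeks, 6 months, 12 months, 18 months, 24 months". Pregnancy is listed as one point, and 2.9.1 repeats this.
- **Role of maternal diet (Table 1).** The row "Maternal diet in pregnancy^2" carries the footnote for a secondary effectiveness outcome. Its measure is a "Diet quality score" from a diet screener. Section 2.2.1 lists it among the secondary outcomes as well.
- **Adjustment (2.9.1).** Confounding from the lack of randomisation, "e.g., household size and income, parental education, ECEC status (public or private), will be assessed and adjusted for using regression models".
- **Selection (3 Discussion).** "selection bias at recruitment between intervention and control sites may bias intervention estimates".

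**The concern.** There is one municipality per arm and no randomisation, so the causal reading of the main estimate depends on what is adjusted for. A pretest of the outcome would normally carry much of that load. Section 2.3 relies on a pretest, and the sample-size argument in 2.5 borrows a difference in change from baseline (+0.46 vegetable items per day). The fully exposed children were not born at their family's pretest, so they have no baseline intake.

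The closest substitute is the mother's diet score. It covers the same domain as the primary outcome, is taken before access and is due in both municipalities. The article gives it no baseline role and labels it an outcome. On the listed schedule, access cannot have affected it in these women. A difference between municipalities in this value would show baseline imbalance, not an effect.

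The two sites also recruit on different terms. Enrolment leads to a nutrition resource in one municipality and only to questionnaires in the other. If this draws families with different interest in diet, the difference can pass into the child vegetable, fruit, pulse and sugary-drink contrasts.

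**Working it through.** **Step 1. Is the score a baseline value for the main-comparison families?** Full exposure requires entry in pregnancy. Access follows the first age-specific questionnaire, and pregnancy is a single listed point. For these women the pregnancy questionnaire is therefore the pretest. Controls who enrol in pregnancy complete the same one. Families who enrol after birth have no such pretest value.

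**Step 2. The plan's own figure.** Section 2.5 states a detectable difference of 0.5 items/day with 100 fully exposed participants, alpha 0.05 and 80% power. It gives no SD, comparator number or sidedness, so the figure cannot be reproduced. It can only be inverted (two-sided, normal approximation):

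- SD = 0.5 / [(1.960 + 0.842) × √(1/n₁ + 1/n₂)]
- 100 vs 100: 0.5 / (2.8016 × 0.1414) = 1.26
- 100 vs 510 (the lower anticipated total per municipality): 0.5 / (2.8016 × 0.1094) = 1.63

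**Step 3. Possible bias.** Let d be the imbalance in maternal diet in SD units and r its correlation with child vegetable intake, both after the named covariates. Then bias = r × d × SD. The documents give neither r nor d; both are assumptions. With b the bias and 100 per group, SE = 1.262 × √(2/100) = 0.178. The true two-sided error rate of a nominal 5% test is Φ(b/SE − 1.96) + Φ(−b/SE − 1.96).

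| r | d | Bias (items/day) | Share of 0.5 | Error rate, 100 per group | Error rate, 160 per group |
|---|---|---|---|---|---|
| any | 0 | 0 | 0% | 5.0% | 5.0% |
| 0.2 | 0.1 | 0.025 | 5% | 5.2% | 5.4% |
| 0.3 | 0.2 | 0.076 | 15% | 7.1% | 8.4% |
| 0.4 | 0.3 | 0.151 | 30% | 13.6% | 18.9% |

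At SD 1.63 the same r and d give 0.03 to 0.20 items/day.

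**Step 4. Precision gained by adjustment.** Adjusted SD = 1.262 × √(1 − r²). Power for 0.5 items/day at 100 per group rises from 80.0% to 81.6% (r = 0.2), 83.6% (0.3) and 86.4% (0.4).

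**Step 5. Precision that may be lost.** The adjusted model can use only controls enrolled in pregnancy. If the plan would otherwise use all controls, moving from 100 vs 510 to 100 vs 100 multiplies the SE by 0.1414 / 0.1094 = 1.29. Adjustment at r = 0.4 multiplies it by √(1 − 0.16) = 0.917. The net factor is 1.19, a wider interval. If the comparison already uses only pregnancy enrolees, this loss does not arise.

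**The case against.** The strongest reply is that the confounder list is introduced as examples. Nothing in it excludes maternal diet, and an article may leave the full covariate set to an analysis plan that is not shown. This stands: a reader might infer that adjustment is limited to socio-demographic factors, and the text does not say so. A reader might also infer that the outcome label keeps the score out of the model. No section says that either, and a pre-access value of an outcome is often used as a covariate. What remains is narrower. The article does assign this variable a role, and on the listed schedule that role does not suit the families in the main comparison.

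Second, 2.9.1 plans a comparison within the intervention municipality, with about 100 unexposed pairs, to probe residual confounding. Those pairs joined under the same offer, so it addresses the self-selection described here. It is a sensitivity analysis, however: it may reveal bias but does not correct the main estimate.

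Third, the Introduction reports large socio-economic differences in diet during pregnancy, so adjustment for education and income already removes part of any imbalance. That is correct, and it is why d in the calculation is the imbalance that remains.

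Fourth, Figure 4 is not shown, so a second questionnaire in pregnancy cannot be ruled out. The text lists one. The fix allows for either case.

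Finally, restricting controls may cost more precision than adjustment gains. That also stands if all controls would otherwise be used (Step 5).

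**Conclusion.** The point holds as a risk that the plan can reduce cheaply. It is not a demonstrated bias. A reader might conclude that diet-related selection definitely stays in the primary estimate; the documents do not support that, because they give neither the correlation nor the imbalance, and the bias is zero if no imbalance remains. What they do support is that no diet measure is among the named confounders and that the one listed pre-access diet score for this group appears only as an outcome.

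Under the assumed ranges the bias is about 0.03 to 0.15 items/day, or 5% to 30% of the 0.5 used for planning. The corresponding error rate is 5.2% to 13.6% with 100 per group. These figures rest on SD 1.26, which itself assumes 100 per group and a two-sided test. The case for the change is protection against bias; the precision gain is modest and may be reversed by the smaller control set.

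**What to change.** In 2.9.1, or in the analysis plan that expands it:

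1. Name the pre-access maternal diet quality score, with gestational age at completion, as a baseline covariate in the main-comparison models for the four primary intakes. Apply this to pairs enrolled in pregnancy in both municipalities. Gestational age is needed because women may enrol at any time in pregnancy.
2. Report the estimate with and without the score in that same set of pairs. If a comparison with all controls is planned, show it alongside, so that the effect of adjustment is not confused with a change of sample.
3. Do not use any maternal diet value taken after access as a covariate.
4. Do not analyse the pretest score as an effect of access. State in Table 1 or its footnote that for women enrolled in pregnancy this value is a baseline measure.

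The change needs wording only, since both municipalities already receive the questionnaire. The costs are that controls enrolled after birth cannot enter the adjusted model, which may widen its interval, and that missing scores need imputation. Measurement error in a short screener will leave some of the confounding in place.

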### 2.3 Study design

In this hybrid type 1 mixed methods implementation study we use a quasi-experimental design. The CONSORT Extension for pragmatic trials with its checklist was used (47). A single intervention municipality will be given access to the Nutrition Now resource and another control municipality (non-equivalent control) will continue as normal (**Figure 2**). Data from participants resident in the intervention municipality will be collected in the form of a pretest before they are given access to the Nutrition Now resource. Subsequently post-test data will be collected until the child reaches 2 years of age (See Data collection). Participants in the control municipality will be asked to provide pre- and post-test data but will not receive access to the Nutrition Now resource. Additionally, a time-series design will be used for comparisons within the intervention municipality between groups of participants exposed to the Nutrition Now resource at different levels of duration, and different types of exposure (See Data collection).

Enrolment started September 2022. The anticipated recruitment period is from September 2022-to April 2023, and we envision that the last participant (if recruited in early pregnancy in April 2023) will complete the study in September 2025. The ECECs were recruited prior to September 2022 and MCH personnel and parents will be recruited autumn 2022.

Intervention municipality provision of access to the Nutrition Now resource starts upon enrollment in the study and is expected to continue beyond the study period as long as the municipality finds it useful.

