	#29 Develop educational materials	Implementation researchers in collaboration with web designer	Develop video and supporting written material to support staff: A short manual for MCH nurses and midwives briefly explaining how to convey the content and use of the e-learning resource to parents. Small information cards with QR codes leading parents directly to the e-learning resource. Educational videos explaining rationale and how to use the resource	MCH nurse and midwives Pregnant women and parents of infants and toddlers	Feasibility	Pre implementation phase 1. Post phase 1 to develop for phase 2. 3 days of work for two researchers and 2 days for web-designer	Need for instructional materials that make it easier for staff to convey the Nutrition Now resource and for pregnant women and parents to learn about how to use the resource
	#31 Distribute educational materials	Implementation researchers	Distribute educational material in person in connection with educational meetings	MCH nurse and midwives	Fidelity Feasibility	Pre-implementation. 2 days of work for 2 researchers	Provide educational materials to staff to facilitate delivering the intervention
**Support clinicians**	#58 Remind clinicians (including end-users of the e-learning resource)	Implementation researchers	Conduct follow-up meetings every six months Reminder e-mails with new resource content at regular intervals	MCH nurse and midwives Pregnant women and parents of infants and toddlers	Adoption Sustainability	Throughout implementation One day work for two researchers	Help MCH staff to recall information and/or prompt them to use the e-learning resource.

**Table 5 T5:** Implementation strategies targeting Nutrition Now implementation delivered through Early Childhood Education and Care (ECEC).

Category (55, 56)	Strategy (# denotes ERIC implementation strategy) (57)	The Actor *(deliver strategy)*	The Action *(specific action, steps or process)*	Action target *(affected by strategy)*	Implementation outcome(s)	Temporality and Dose	Justification

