** **	#31 Distribute educational materials	Implementation researchers	Distribute educational material digitally and by mail	ECEC leaders and champion	Fidelity Feasibility	Pre implementation	Provide educational materials to staff to facilitate delivering the intervention
**Support clinicians **	#58 Remind clinicians	Implementation researchers	Reminder e-mails with new resource content at regular intervals and digital newsletters with support on how to progress with the intervention including change processes among ECEC staff	Champions at ECEC	Adoption Sustainability	During implementation	Help ECEC staff to recall information and/or prompt them to use the e-learning resource
**Engage consumers**	# 41 Involve patients/consumers and family members	ECEC leaders	Post URL to parent part of the e-learning resource on ECEC website	ECEC parents	Feasability Adoption	Start of the implementation, one time	Create synergy that enhance ECEC staff’s motivation to follow up the implementation
**Change Infrastructure**	# 44 Mandate change	ECEC champions	ECEC champion lead and holds meetings with ECEC staff regularly	ECEC staff	Adoption Feasability Sustainability	During implementation	Create structures (e.g., staff meetings) that enhance the implementation

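### The within-municipality comparator pairs lack only the parent components: most may already have met the resource through ECEC, which weakens the check on residual confounding

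*Protocol article*

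**What the plan says.** Section 2.9.1 makes the contrast between children given all components and the control municipality the main comparison. It adds a second contrast inside the intervention municipality, against "approximately 100 parent-offspring pairs completely unexposed to the Nutrition Now resource as a result of the recruitment design", and gives its purpose: "In this example they act as a sensitivity analysis to assess bias from residual confounding".

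The legend and text around Figure 4 (section 2.8) describe one group that stays without parent access through its last assessment: "Two-year-olds recruited at the regular health visit will be given access to the" toddler component only once the 24-month questionnaire is done. Parents "will be recruited from October 2022 until April 2023 through the MCH centre route"; section 2.3 puts the start a month earlier ("The anticipated recruitment period is from September 2022-to April 2023").

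On the ECEC side, the same legend says that "ECEC staff will be recruited and complete the pretest questionnaire in September 2022, before getting access to the Nutrition Now-recourse". The Introduction names ECEC departments for ages 1-3 as a delivery channel. Section 2.8 treats this as exposure, since a one-year-old in ECEC also receives the preschool component. Table 2 gives ECEC attendance at 1-2 years as 85% in the intervention municipality. Section 2.5 limits staff participation to ECECs whose leader consents.

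**The concern.** The comparator is defined by the date on which the parent gained access. The resource reaches the child by two routes, parent and ECEC, and the ECEC route opens at or before the start of this group's recruitment. Nothing in the article keeps children in participating ECECs out of the comparator. The confounders listed in section 2.9.1, given as examples, mention ECEC only by public or private status, which does not measure exposure.

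With one municipality per arm, place and treatment cannot be separated in the main comparison, so this internal contrast is the only stated design check on residual confounding. If the supposedly untreated children are partly treated, the two estimates can differ for a reason unrelated to confounding, and the planned reading of a difference would be wrong. The component and duration comparisons in sections 2.3 and 2.9.1 could inherit the same misclassified zero-exposure group.

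**Working it through.** **The protocol's own count.** Births per year (about 400, section 2.5) × recruitment period in years × participation (50%, section 2.5):

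400 × 6/12 × 0.50 = 100.

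This reproduces the stated figure. At 80% participation it gives 160, so the same arithmetic yields the 100-160 fully exposed children in section 2.5. Counting seven calendar months gives 400 × 7/12 × 0.50 = 117. The match supports reading the 100 pairs as the 24-month entrants.

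**Time available for ECEC exposure.** ECEC access follows the September 2022 pretest. The 24-month questionnaires of new entrants run from September or October 2022 to April 2023. The lag is about 1-7 months if ECEC access began in September and parent recruitment in October, and about 0-7 months if ECEC access began in October or parent recruitment in September. With even recruitment over 0-7 months the mean is about 3.5 months.

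**How many children.** Let p be the share of ECEC attenders who are in a participating ECEC (not stated, so assumed). Possibly exposed children per 100 = 100 × 0.85 × p:

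- p = 0.25: 21
- p = 0.50: 42.5
- p = 0.75: 64
- p = 1.00: 85

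**Effect on the contrast.** Let s be the share of the full effect that the ECEC route has already produced in those children (also assumed). Starting from the 0.5 items/day used in section 2.5:

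observed difference = 0.5 × (1 − 0.85 × p × s).

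The article gives no SD. Solving its statement (0.5 items/day, alpha 0.05, 80% power) for 100 versus 100, two-sided:

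SD = 0.5 / [(1.960 + 0.842) × √(2/100)] = 1.26.

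A one-sided test would imply 1.42, and 100 versus 510 would imply 1.63. Power below uses 1.26 and 100 per group.

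| p | s | Attenuation | Observed difference | Power |
|---|---|---|---|---|
| 0.25 | 0.25 | 5% | 0.47 | 76% |
| 0.50 | 0.50 | 21% | 0.39 | 60% |
| 0.75 | 0.50 | 32% | 0.34 | 48% |
| 1.00 | 0.50 | 43% | 0.29 | 36% |

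If s = 0 there is no attenuation. The algebraic limit, p = 1 and s = 1, gives 0.075 items/day, but it requires every ECEC to take part and the ECEC route alone to deliver the whole effect.

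**The case against.** The strongest reply is that this is a supporting analysis. The protocol offers it as triangulation between designs with different biases and does not claim that it is free of bias. It also recognises ECEC exposure as conditional, plans comparisons by type and duration of exposure, and logs use of the resource. Coding each 24-month entrant by ECEC could be left to an analysis plan that is not shown, and Figure 4 itself is not visible.

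Much of that stands, and it lowers the severity. It does not remove the point. The article asserts that these pairs had no exposure at all and builds an inference on that assertion, while its own delivery dates say otherwise. That is a wrong statement, not an omitted detail.

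A reader might also infer that parents in this group could reach the resource before their questionnaire, because Table 5 has ECECs "Post URL to parent part of the e-learning resource on ECEC website" and Table 4 lists "Small information cards with QR codes leading parents directly to the e-learning resource". The documents do not support that. Section 2.5 sends all recruitment routes to a registration website, and section 2.8 opens access only after the age-specific questionnaire. Neither table says this gate is bypassed. Nurse training and newspaper or website publicity are not exposure either, because the estimand concerns access to the resource.

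**Conclusion.** The point holds for exposure through ECEC. The comparator pairs are unexposed to the parent components but cannot be called wholly unexposed. Up to about 85 of 100 may have had roughly 0-7 months of the ECEC component. This is an upper bound: 85% is attendance, ECEC participation is not given, and uptake and fidelity within participating ECECs are themselves study outcomes (Table 1).

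The size of the distortion cannot be fixed from the article. The range of 0.47 to 0.29 items/day rests on assumed values of p and s.

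Two stronger readings are tempting and go too far. The first is that the check is biased towards no effect overall. Shrinkage follows only for this contamination, and only if the ECEC component changes diet within the lag. Calendar time may push the contrast either way, since the comparator is assessed in 2022-23 and the last fully exposed children finish in 2025. The second is that the main result is undermined. The between-municipality comparison does not use these pairs as its reference. What is at risk is the reading of the residual-confounding check and of the component and duration comparisons, so this is a moderate point.

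**What to change.** 1. In section 2.9.1, replace the claim of complete non-exposure with a statement that these pairs are unexposed to the parent components.
2. For each 24-month entrant, record the ECEC attended (or none), whether it participates, and the months from its access date to the questionnaire.
3. Keep the sensitivity analysis, with ECEC exposure in the model as yes/no and as months. If all ECECs gained access in the same month, months of exposure will track calendar date among attenders of participating ECECs; say so when reporting.
4. Repeat the check in children who are not in a participating ECEC, or who were assessed before it had access, and report it beside the modelled analysis.
5. State in advance that a gap between the within- and between-municipality estimates may reflect ECEC exposure or calendar time as well as confounding.

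The cost is one or two questionnaire items, a list of ECEC access dates, and a change of wording. The restricted reference will be smaller: 100 − 85 = about 15 pairs if every ECEC takes part, more if fewer do or if some children were assessed before access. It is also selected on ECEC attendance, which can bring in confounding of its own, so it should not replace the modelled analysis.
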